### Participant timeline {13}

The participant timeline is shown in Fig. 1.

### Sample size {14}

The sample size was calculated based on a previous study in the literature [16, 17] (Fig. 2), considering the expected difference and standard deviation and weighting colony-forming units (CFU) of bacteria. For the statistical calculation, paired samples were considered, with α=5% and an 80% test power. The minimum number in this clinical trial was determined to be 34 teeth per group. Therefore, 40 teeth per group will be recruited to compensate for possible dropouts during the experimental period. G*Power 3.1 was used to perform the calculations (Fig. 3).

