**Methods:**

A total of 160 teeth with deep occlusal dental caries will be selected and divided into 4 groups: G1 - control group (Caries removal with a low-speed drill); G2 - Partial Caries Removal with Papacarie™ (Fórmula e Ação, São Paulo, SP, Brazil); G3 - Partial Caries Removal with Papacarie™ and application *Bixa orellana* extract (20%) (Fórmula e Ação, São Paulo, SP, Brazil); G4 - Partial Caries Removal with Papacarie™ and application *Bixa orellana* extract (20%) with LED (Valo Cordless Ultradent®, South Jordan, UT, USA) (aPDT). After treatment, all the teeth will be restored with glass ionomer cement and followed up clinically and radiographically, with evaluations at immediately, 1 week, and 1, 3, 6, and 12 months. Dentin samples before and after treatment will be analyzed microbiologically. The efficacy of treatments will be assessed with microbiological (colony-forming units, before and after carious tissue removal), radiographic (integrity of the periapical area and eventual changes in the radiolucent zones), and clinical examinations (retention of the restorative material in the cavity and occurrence of secondary caries), as well as with the time required for the procedures and the need for anesthesia during the procedures. In case data distribution is normal, analysis of variance (ANOVA) will be used for both the dependent and independent variables. In case the data distribution is not normal, the Friedman test will be used for the dependent variables. For independent variables, the Kruskal-Wallis test will be used.

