### Trial design {8}

This is a study protocol for a randomized (1:1), single-blind (outcome assessors, only), parallel groups, equivalence, one-center, phase 2, controlled clinical trial. Figure 1 shows a schematic diagram and is the Standard Protocol Items: Recommendations for Interventional Trials (SPIRIT) figure.

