## Interventions

### Explanation for the choice of comparators {6b}

The use of a drill, which is the conventional and most commonly used method, will be compared with the use of Papacarie™ with or without the *Bixa orellana* extract, and with or without the irradiation for aPDT. This study will show which of these treatments will be more efficient with regard to microbiological, radiographic, and clinical aspects. The models, types, and details of all instruments have been detailed upon the first appearance in the text.

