### Methods in analysis to handle protocol non-adherence and any statistical methods to handle missing data {20c}

No losses greater them 5% of the sample are expected, and if they happen, pairwise deletion will be used.

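### The 34 teeth per group come from a paired-samples calculation, so the stated 80% power is not established for any comparison between the four independent arms

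*Protocol article*

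**What the plan says.** Sample size {14} bases the number on earlier literature, "considering the expected difference and standard deviation and weighting colony-forming units (CFU) of bacteria". It then gives the model, "For the statistical calculation, paired samples were considered, with α=5% and an 80% test power", and the result, "The minimum number in this clinical trial was determined to be 34 teeth per group". The allowance for losses follows: "40 teeth per group will be recruited to compensate for possible dropouts during the experimental period". The expected difference, the SD and the sidedness of the test are not in the text. The section points to Figures 2 and 3, which are not shown.

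The design is described elsewhere in the same article:

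- Trial design {8} calls it a "parallel groups, equivalence, one-center, phase 2, controlled clinical trial".
- The Abstract says: "A total of 160 teeth with deep occlusal dental caries will be selected and divided into 4 groups".
- The inclusion criteria intend only one tooth per child.
- Under Sequence generation {16a}, each child draws an envelope that holds one of the four groups.
- Explanation for the choice of comparators {6b} promises: "This study will show which of these treatments will be more efficient with regard to microbiological, radiographic, and clinical aspects".
- Statistical methods {20a} plans ANOVA, or Kruskal-Wallis followed by Mann-Whitney, for independent variables. It plans Friedman followed by Wilcoxon for dependent ones.

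**The concern.** A paired calculation uses the SD of within-pair differences and n pairs. A comparison of two arms uses the SD between teeth and n teeth in each arm. The two give different power for the same n, and the sample size section does not say how one was turned into the other.

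If the pairing is before versus after, the mismatch is also one of substance. Every arm removes carious tissue, so counts can be expected to fall in each. Power to detect that fall is not power to separate photodynamic therapy from the drill, from the gel alone, or from the gel with extract. The four arms and their six possible pairs do not enter the calculation as described.

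At stake is how a null result would be read. A reader will take the 80% as covering the treatment comparison, so a non-significant difference between groups 4 and 3, or 4 and 2, could pass as evidence of no added benefit from an adequately powered trial.

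**Working it through.** **Inputs.** From Sample size {14}: paired model, alpha 0.05, power 0.80, 34 per group, 40 recruited. From Trial design {8} and the Abstract: four parallel groups. Assumed, because not in the text: two-sided tests, normal data, equal SDs.

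**1. What paired effect gives 34?** The power of a paired t test is P(|T| > t₀.₉₇₅,ₙ₋₁), where T is noncentral t with noncentrality dz·√n and dz = mean difference / SD of the differences. At dz = 0.50 and n = 34 the noncentrality is 0.50 × √34 = 2.92, the critical value is 2.03 and power is 80.8%. At n = 33 power is 79.5%. So dz = 0.50 gives 34, as does any dz from 0.495 to 0.503. A one-sided test gives 34 for dz from 0.435 to 0.442. This is a back-solution with one free quantity. It shows that 34 is consistent with a paired test at about 0.5, and it does not reproduce the figure from stated inputs.

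**2. Two independent arms, difference 0.50 SD.** The noncentrality is d·√(n/2) with 2n − 2 degrees of freedom.

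- 34 per arm: 0.50 × √17 = 2.06, critical value 2.00, power 53%.
- 40 per arm: 0.50 × √20 = 2.24, critical value 1.99, power 60%.
- 80% power needs 64 per arm.

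**3. Sensitivity to how the paired effect translates.** Suppose the raw paired difference is also the raw difference between two arms on post-treatment values. With correlation ρ between paired values, SD of differences = SD·√(2(1 − ρ)), so d = 0.50·√(2(1 − ρ)).

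| ρ | d | Power, 34 per arm | Power, 40 per arm |
|---|---|---|---|
| 0 | 0.71 | 82% | 88% |
| 0.3 | 0.59 | 67% | 74% |
| 0.5 | 0.50 | 53% | 60% |
| 0.7 | 0.39 | 35% | 40% |
| 0.9 | 0.22 | 15% | 17% |

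Adjusting for the baseline count divides d by √(1 − ρ²). Over the same correlations, power then runs from 82% to 55% with 34 per arm and from 88% to 62% with 40. In every row the between-arm difference is as large as the whole paired difference.

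**4. Detectable difference between two arms.** Solving the formula in step 2 for d at 80% power needs only n and alpha, and nothing from the figures that are not shown.

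| Two-sided alpha | 34 per arm | 40 per arm |
|---|---|---|
| 0.05 | 0.69 SD | 0.63 SD |
| 0.05/6 (Bonferroni, all six pairs) | 0.87 SD | 0.80 SD |

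The missing-data section says: "No losses greater them 5% of the sample are expected". A 5% loss would leave 40 × 0.95 = 38 per arm, so the 34 and 40 columns bracket the expected number.

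**The case against.** The strongest reply is that the deciding inputs sit in figures that cannot be seen. A reader might infer that the trial lacks 80% power between arms. The text does not support that: if two arms differ by 0.69 SD or more with 34 per arm, or 0.63 SD with 40, the power is there, and nothing visible rules out such a difference. The same holds for reading 53% as the power of this trial. It carries a back-solved within-pair effect over to a differently scaled between-arm effect, and step 3 shows how far the answer moves. Both objections stand, so the size can be given only as a conditional range.

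A reader might also take it as fact that the calculation was before versus after within one arm. The text says only that samples were paired, and the pairing in the source study is not shown. With one tooth per child, before and after in the same tooth is the only pairing visible here for colony counts, but it remains an inference.

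Paired data do belong to this trial. Counts are taken before and after treatment, paired tests are planned for dependent variables, the null hypothesis names no comparator, and the sample size section never says that the 80% refers to a contrast between arms. That is a reason for a modest correction, stating which comparison the figure covers. It does not remove the mismatch, because the comparators section promises a ranking of treatments and the text gives no sample size for one.

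Finally, Statistical methods {20a} states no Bonferroni correction, so the six-pair figures only illustrate what such a correction would cost.

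**Conclusion.** The point holds as a mismatch between the sample size model and the design and planned tests. No sum in the section is shown to be wrong. That the described calculation does not establish 80% power for a between-arm comparison follows from the article's own text and does not depend on the missing figures. The detectable differences of 0.63 SD (40 per arm) and 0.69 SD (34) are equally independent of them, given a two-sided 5% t test.

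The size of any shortfall is conditional on two assumptions: a paired effect of about 0.50, and a rule for turning it into a between-arm effect. Under the equal-effect rule power is 53% to 60%. Under the carried-over raw difference, only a within-pair correlation near zero keeps 80% with 34 per arm. The statement deserves correction before results are reported, because it is the trial's only power claim and concerns a primary outcome.

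**What to change.** Keep 40 teeth per arm and reword the sample size section in three respects.

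1. Say what was paired, give the difference, SD and sidedness in the text, and state that the 80% applies only to that paired comparison.
2. Add the between-arm figure, for example: With 40 teeth per arm (34 evaluable), a two-sided 5% comparison of two arms has 80% power for a difference of 0.63 SD (0.69 SD) on the scale on which CFU are analysed; with Bonferroni correction for all six pairs, 0.80 SD (0.87 SD).
3. Say whether a difference of that size is plausible and worth detecting. The detectable difference alone does not show this.

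The added sentence concerns detecting a difference. It does not settle the equivalence label in Trial design {8}, which would need its own power statement if equivalence is really the aim.

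The cost is rewording one section and a less favourable stated figure. No participants are added and no procedure changes.

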**Fig. 2 Fig2:**
[figure not shown]
Sample size calculation used for this clinical research

**Fig. 3 Fig3:**
[figure not shown]
Determination of the sample size for this clinical research in G*Power 3.1

### Recruitment {15}

As participants will already be in pediatric dentistry treatment, we believe recruitment will be feasible. Participants will be approached at their usual clinic appointment. We believe participants will be present for the follow-ups due to concerns and other possible treatments in the clinic.

## Assignment of interventions: allocation

### Sequence generation {16a}

Block randomization will be performed using the website randomizer.org, which will generate 4 sets of numbers, according to the number of research groups and participants. Opaque envelopes will then be ordered, with the corresponding groups written inside, and kept in a locked room inside the clinic, accessible only to the researchers. A researcher who will not be involved in the data collection will be responsible for generating the sequence and making and sealing the envelopes. The participant will remove the envelope at the time of treatment.

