### Intervention description {11a}

*Group 1 –* Caries removal with a low-speed drill (control group):Initial periapical radiography (Children's Insight IP-01 Periapical – Carestream, Rochester, Nova York, EUA);Prophylaxis with a toothbrush and fluoride toothpaste (Colgate® Children [name], Nova York, EUA) and fluoride toothpaste (Herjos Prophylactic Paste, Vigodent, Rio de Janeiro, Brazil);Relative isolation with cotton roll (Dental Roller Cotton – Cremer, Santa Catarina, Brazil) and aspirator (Disposable Dental Sucker – SSPlus, Paraná, Brazil);Microbiological sampling with ear curette (Meyhoefer auricular n° 2 curette (ABC Instrumentos Cirúrgicos, São Paulo, Brazil) for standardization of volume of carious tissue;Removal of carious dentin with carbide burs (Carbide Drill No. 6 Spherical CA – Angelus, Paraná, Brazil) and manual instruments (Double Dentin Digger n° 17/18 - Millennium – Golgran, São Paulo, Brazil);Second microbiological sampling with ear curette (Meyhoefer auricular n° 2 curette (ABC Instrumentos Cirúrgicos, São Paulo, Brazil) for standardization of volume of carious tissue;Clinical inspection of texture of the remaining dentin with an exploratory probe (Eighth Exploration Probe – Golgran, São Paulo, Brazil), to check the absence of soft tissue;Restoration with glass ionomer cement (Ketac Molar EasyMix – 3M ESPE); andClinical inspection for signs of infiltration and radiographic follow-up immediately, 1 week, and 1, 3, 6, and 12 months after treatment.

*Group 2 –* Partial removal of carious tissue with the administration of Papacarie™:Initial periapical radiography;Relative isolation with a cotton roll and aspirator;Microbiological sample with otoscope curette to standardize the volume of carious tissue;Application of Papacarie™ (Fórmula e Ação, São Paulo, SP, Brazil) for 5 min, removal of carious tissue around lateral walls of the cavity with a noncutting curette and no removal of carious tissue on pulp floor (partial removal) [10];Washing of the cavity with water and drying with absorbent paper;Second microbiological sampling;Clinical inspection of texture of the remaining dentin with an exploratory probe, to check the absence of soft tissue;Restoration with glass ionomer cement (Ketac Molar EasyMIx 3M ESPE); andClinical inspection for signs of infiltration and radiographic follow-up immediately, 1 week, and 1, 3, 6, and 12 months after treatment.

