#### Microbiological evaluation

This is one of the primary outcomes of the study. A sample of caries-affected dentin will be taken from each selected tooth before the removal of the carious tissue. The samples will be standardized with the use of a Meyhoefer auricular curette n° 2 (ABC Instrumentos Cirúrgicos, São Paulo, Brazil), because it has a hole in its tip, and placed into test tubes containing 3.8 ml of the transport medium (Phosphate Buffered Saline (PBS) - Thermo Fisher Scientific, Massachusetts, EUA). The dental tissue will be dispersed in the transport tube (Microtubo Tipo Eppendorf Cap. 1.5 ml – GlobalPastic, São Paulo, Brazil) containing glass pearls through agitation at maximum speed in a vortex device (Agitador Para Tubos Vortex – Kasvi, Paraná, Brazil) for 30 s to homogenize the biological material. The biofilm will be diluted in series on the order of 10^1^ to 10^6^ in peptone water and inoculated in culture media in Petri dishes (Placa de Petri Descartável Estéril - PRO-LAB MATERIAIS PARA LABORATORIOS LTDA, São Paulo, Brazil). Aliquots of dilutions 10^4^, 10^5^, and 10^6^ will be sewn on the surface of Brucella agar (Difco Laboratories, Detroit, Michigan) containing defibrinated sheep blood (50ml/L), hemin (5 mg/ml), and menadione (10mg/ml) for the determination of the total number of viable microorganisms (VM). Aliquots of dilutions 10^3^ and 10^4^ will be sewn on Mitis Salivarius agar (Difco Laboratories, Detroit, Michigan) for the determination of the total number of streptococcus (S). Aliquots of dilutions 10^1^ and 10^2^ will be sewn on Mitis Salivarius agar with the addition of debacitracin for the determination of the population of streptococcus of the mutans group (SM).

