### Implementation {16c}

The researchers responsible for the treatment application will enroll participants and assign participants to interventions, only the outcome assessors will be blind. The allocation sequence will be made by a different researcher, who will not be involved in the procedures.

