## Assignment of interventions: blinding

### Who will be blinded {17a}

The clinical evaluations of the carious tissue removal, as well as the microbiological and radiographic analyses, will be performed by examiners blinded to the treatments performed on each tooth. Only the researcher in charge of procedures will know to which group the participants belong.

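### The baseline dentin sample is a step inside each arm's procedure and nothing places it before the envelope is opened, so it can be taken with the arm known and after unequal preparation

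*Protocol article*

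**What the plan says.** Sequence generation {16a} describes the envelopes ("Opaque envelopes will then be ordered, with the corresponding groups written inside") and says when they are used: "The participant will remove the envelope at the time of treatment". Implementation {16c} gives enrolment, assignment and treatment to the same people: "The researchers responsible for the treatment application will enroll participants and assign participants to interventions, only the outcome assessors will be blind". Who will be blinded {17a} adds: "Only the researcher in charge of procedures will know to which group the participants belong". The blinding in that section covers the clinical evaluations and the microbiological and radiographic analyses.

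Intervention description {11a} sets out one list of steps per arm. In Group 1 the first sample appears as "Microbiological sampling with ear curette". In Groups 2, 3 and 4 it appears as "Microbiological sample with otoscope curette to standardize the volume of carious tissue". The Group 1 list has an earlier step, "Prophylaxis with a toothbrush and fluoride toothpaste", which the other three lists lack.

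The Microbiological evaluation section, which calls this a primary outcome, fixes the timing of the first sample only relative to excavation: "A sample of caries-affected dentin will be taken from each selected tooth before the removal of the carious tissue".

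**The concern.** The primary microbiological comparison has a before count and an after count. The before count is useful as a baseline only if the allocation cannot influence it. If the person holding the curette already knows the arm, the choice of where in the lesion to sample, and how deep, can differ between arms without any intent. Richer dentin at baseline in one arm makes that arm's reduction look larger although the treatment did nothing more. Plate counting by a blinded examiner cannot undo this, because the difference is already in the tube.

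The same applies if one arm's tooth is cleaned with fluoride paste before sampling and the others are not. A baseline collected in this way is also weaker evidence that the arms were comparable at the start.

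**Working it through.** The plan gives no figure on this point, so there is none to reproduce. The check is to set the sections side by side.

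**1. Steps listed up to and including the first sample (Intervention description {11a})**

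| Arm | Steps in the order listed |
|---|---|
| Group 1 | radiograph, prophylaxis, isolation, first sample |
| Groups 2, 3, 4 | radiograph, isolation, first sample |

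Followed literally, the operator has to know after the radiograph whether to carry out prophylaxis. That depends on the arm, so the arm must be known before the first sample. If the prophylaxis difference is only a drafting slip, this step of the argument drops out. The first sample then still sits inside the allocated procedure in all four lists.

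**2. Does any section put the sample ahead of the envelope?** Sequence generation {16a} ties the envelope to treatment and places no study step before it. Concealment mechanism {16b} and Implementation {16c} give no order of steps. Microbiological evaluation requires only that the sample come before excavation. None of them puts sampling first.

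**3. Does any section blind the sampler?** No. {17a} blinds the people who evaluate and analyse. {16c} limits blinding to outcome assessors, and the researcher in charge of procedures knows the group. The person who takes the dentin is not named anywhere.

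**4. What does the curette control?** Intervention description {11a} and Microbiological evaluation present it as a way to standardise the sample, and {11a} specifies volume. The outcome section names one curette for all teeth, so I read the different names in the arm lists as wording only. Volume is addressed; site and depth are not.

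**5. How many samples?** 40 teeth per group × 4 groups = 160 first samples.

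**6. How would a shift carry through?** Let B and A be the before and after counts, and suppose the baseline yield in one arm is multiplied by k.

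- Log reduction: log10(kB) − log10(A) = [log10(B) − log10(A)] + log10(k). The whole of log10(k) enters as bias.
- Assumed k = 1.25: log10(1.25) = 0.10. Assumed k = 2: log10(2) = 0.30.
- Proportion measures such as % SM/VM: kSM / kVM = SM / VM. A uniform shift in yield cancels. A shift that changes the mix of organisms, for example from sampling at another depth, would not cancel.

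The range of k is an assumption with no support in the documents, and the article does not specify a log10 reduction as the endpoint. The figures show only how a shift would pass through.

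**The case against.** The strongest reply is that the order is never stated. The envelope sentence does not rank opening against sampling. The abstract and the specific objectives describe dentin samples or counts on either side of treatment, which fits a first sample taken before treatment starts. The SPIRIT timeline figure, which might settle the order, is not shown. The arm lists are whole care pathways: they begin with a radiograph, although eligibility already relies on a radiographic examination, and they end with 12-month follow-up. Appearing in a list therefore does not prove that a step follows allocation. The sampler is not named, the curette controls volume, and the second sample is taken after treatment in any case.

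Most of this stands, and it limits how firmly the point can be put. A reader might infer that the operator certainly knows the arm at all 160 baseline samples, or that the CFU reduction is biased by 0.10 to 0.30 log10. The documents support neither: the first is an inference from the lists, the second only restates an assumption.

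Two parts of the reply do not carry. Saying that the sample precedes treatment does not say that it precedes the envelope. And the Group 1-only prophylaxis cannot be put down to the remark in Explanation for the choice of comparators {6b} that details are given at first mention, because that remark concerns instruments, not steps. The exposed second sample is no reason to leave the first one exposed, since only the first can be protected by moving the envelope.

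**Conclusion.** The point holds in a limited form. On the plain reading, the baseline CFU sample for a primary outcome can be taken with the arm known and after preparation that differs between Group 1 and the rest. No section rules this out. Up to 160 samples are affected if the lists are followed as written.

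The size of any bias is unknown. It would bear mainly on absolute CFU of SM and LB, and less on the proportion measures if the shift in yield is uniform. The conclusion assumes that the envelope is opened when it is removed and that the researcher carrying out the procedure also takes the sample. Both are natural readings, but neither is stated. The documents do not show that biased sampling will occur; they show that the order of steps leaves it possible when it is easy to prevent. The change is worth making because it is cheap and protects half of a primary comparison.

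**What to change.** - In Sequence generation {16a}, state that the envelope is opened only after the first dentin sample has been taken and labelled with the participant code.
- In Intervention description {11a}, move all steps up to and including that sample into one block common to the four arms, ahead of allocation.
- Reconcile the prophylaxis step, which only Group 1 lists, so that preparation before sampling is the same in every arm. Which preparation to use is for the investigators to decide.
- Record the time of the first sample and the time of envelope opening on the case report form.
- Trial status gives recruitment from 30 May 2022 to 30 April 2023, so some children may already have been treated. For them, document the order actually used.

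The cost is wording and two extra entries on the form; the visit, staff and sample stay the same. A few children may be sampled and then not randomised. The second sample remains exposed to knowledge of the arm, and this change does not alter that.
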